### Outcomes

All outcomes of the study will be assessed at the starting point, and after 2 weeks and 3 months. Participant characteristics and demographic variables will be collected at baseline. Participant characteristics include age, gender, and relevant comorbidities, while demographic variables include job category, work experience, academic qualification, job title, and the number of local training courses. The outcomes are based on the recommendations of the NPT and its 4 related constructs [58].

#### Primary Outcome

The primary outcome involves the evaluation of the ELNEC-PPC course aimed at providing PC in a range of health care contexts through the Arabic NoMAD questionnaire and observation of routine clinical care.

#### Secondary Outcome

The secondary outcomes involve an interview, operating context examination, and assessment via the NPT toolkit.

### Interview Procedure

Semistructured face-to-face interviews will be conducted with all nurses on successfully completing the ELNEC-PPC web-based training course. All participants have direct contact with patients, and 3 rounds of interviews will be conducted after 3 months. After consenting, participants will be interviewed by the main investigator (MA). All interviews will be audio recorded and transcribed. If participants do not want to be recorded, the main investigator will make notes and then transcribe an in-depth discussion account. Some participants will be interviewed in pairs or small groups. They will be asked about the changes they experienced in terms of care after the training. Throughout the interview rounds, participants will be questioned about the most important developments since the start of the program. They will be asked to disclose their opinions around PPC and to clarify the degree to which they would be implementing the method. Themes are based on the NPT [59] and will be reviewed to include problems from the initial meetings. This will assist researchers in exploring participant views on the simplest models of care.

Consequently, the interactive NPT toolkit will be used. It contains 16 questions for thinking through an implementation problem. The embedding will be improved, and statements and explanations will be edited for a web-enabled tool.

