## Methods

### Trial Design

This study is designed as a multicenter, investigator-blinded, parallel, 3-month, pragmatic, 2-arm, superiority (provision of PPC with usual care is superior to usual care only) RCT, in which different units from multiple hospitals are stratified and randomized. Randomization will be performed as block randomization with 1:1 allocation, and it will be conducted according to the Consolidated Standards of Reporting Trials (CONSORT) guidelines. The CONSORT statement is a guideline designed to improve the transparency and quality of the reporting of randomized trials [49,50].

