The start of the study will involve preparation of formal and essential approvals through the academic professor (HJ) responsible for the CNEU at the Faculty of Nursing and coordination with the Babylon Health Department, to obtain official agreements for sample collection according to the study criteria. The candidate envelopes will be opened and the candidates will be entered in an Excel spreadsheet. The information entered in each form will be added in sequence, and the Excel spreadsheet will be backed up, printed, and kept in a safe and secure location. A copy of the spreadsheet will be sent via email to the main investigator to contact the participants via their provided email addresses or phone numbers (Telegram, Viber, or WhatsApp). The enrollment process is outlined in Figure 1. If candidates are eligible and willing to participate, the informed consent form will be signed and the main investigator will contact each participant and send a link to the web-based baseline questionnaire via email or social communication apps (Telegram, Viber, or WhatsApp). Then, randomization will be performed via a web-based randomization system (see the randomization section).

Participants can return the signed informed consent form in a prestamped envelope provided by the unit or can take a picture of the signed consent form and send it via a text message to the main investigator. Subsequently, the main investigator will contact the participants, inform them about the results of the random distribution, and provide instructions according to the group that was randomly chosen (control or intervention group). All instructions will be completed on the phone or via text message, and participants will receive a link to a website from the main investigator (Multimedia Appendix 7), which provides all instructions and details of participation in the training course (also presented in Arabic).

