### Blinding

This is a single-blinded study, and the participants are not blinded to group allocation. Examination and interpretation of the study results will be achieved by investigators blinded to group allocation. Once the study is completed, a copy of the data will be extracted in a pseudonymized form for statistical analyses. The information concerning the group allocation will be added to the data set with the intervention and control groups categorized as T and C, respectively. This work is done under a camera for documentation later (by supervisors), and the complete data entry is performed with blinding of the main researchers. The randomization key (ie, document with group details) will be kept with supervisors. They will provide the randomization key to the researchers once blinded interpretation of the results is finalized.

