Repeated measures ANOVA will be performed to assess the multivariate main intervention effects (associated with controls) considering pre, post, and follow-up time points, as well as their interface effects. A 2-sided *P* value <.05 will be considered significant. The standardized effect size (Cohen *d*) will also be calculated. Mediator analysis will be controlled to determine which subgroups would benefit further from the intervention, with outcome variables regressing on independent variables, including age group, sex, education, and starting Arabic NoMAD score.

Secondary outcomes will be analyzed using an approach similar to the approach described for the primary outcome with linear mixed models for repeated measures. The data from the 2-week and 3-month follow-ups will also be analyzed using the approach described above for the primary outcome.

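### The interview and toolkit outcomes are given a between-group repeated-measures model that the described data cannot support, and the investigator-blinded label does not match the main investigator's role

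*Protocol article*

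**What the plan says.** **Outcomes and analysis.** Under Primary Outcome, the course is evaluated "through the Arabic NoMAD questionnaire and observation of routine clinical care". Under Secondary Outcome: "The secondary outcomes involve an interview, operating context examination, and assessment via the NPT toolkit". The Outcomes section puts every outcome on one schedule: baseline, 2 weeks and 3 months. Statistical Analysis compares the arms by intention to treat, and its primary estimate is the difference in NoMAD score at 3 months. It then adds: "Secondary outcomes will be analyzed using an approach similar to the approach described for the primary outcome with linear mixed models for repeated measures".

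**Procedures.** Interview Procedure states: "Semistructured face-to-face interviews will be conducted with all nurses on successfully completing the ELNEC-PPC web-based training course". The interviews come in three rounds after 3 months, are held by the main investigator, in some cases with pairs or small groups, and ask how care has changed since the training. The Interviews text under Data Collection repeats most of this but includes every participating nurse. Process of Implementation places workplace monitoring straight after the intervention group's second NoMAD, to gauge what the course did to the nurses' work. It then has the main investigator apply the toolkit after 3 months. Of these 3-month assessments, only the last NoMAD link is expressly sent to both arms.

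**Blinding.** Trial Design calls the study "multicenter, investigator-blinded, parallel, 3-month, pragmatic, 2-arm, superiority". The Blinding section says: "Examination and interpretation of the study results will be achieved by investigators blinded to group allocation". It also says the main researchers are blind during data entry, and it describes an analysis data set "with the intervention and control groups categorized as T and C, respectively". Under Screening for Eligibility and Enrollment, after consent, "the main investigator will contact the participants, inform them about the results of the random distribution".

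**The concern.** A mixed model with group and time effects needs values from both arms at the scheduled times, on a scale defined for each nurse. The interview and toolkit descriptions appear to supply one arm, after the course only, and partly in groups. If so, the named secondary outcomes have no workable between-group analysis, and a contrast limited to nurses who finished the course would not be a randomized one. The observation component would leave the primary outcome without a defined between-group result for that part.

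The blinding statement raises a second, separate issue. Readers would credit the trial with a protection that does not cover the person who collects the interview and toolkit data, and the coding of the analysis file gives little protection to those who interpret the results.

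**Working it through.** **1. Requirement against description (interview and toolkit).**

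| | Outcomes and Statistical Analysis | Process of Implementation, Interview Procedure, Interviews |
|---|---|---|
| Arms | Both | Course completers (Interview Procedure); every participating nurse (Interviews); arm not stated for the toolkit |
| Times | Baseline, 2 weeks, 3 months | After 3 months |
| Unit | Individual nurse | Some nurses in pairs or small groups |
| Assessor | Investigator-blinded trial | Main investigator |

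Under Usual Care, controls receive the course only after the trial. During the trial they cannot be completers, nor can they say what changed after training. So although the Interviews text covers all nurses, its stated aim (success in passing the course) and its questions (changes connected with training) fit only the trained arm.

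**2. What the planned model can estimate.** Statistical Analysis describes a combined intervention-and-time variable with a baseline level shared by the two arms. Written out, with g = 1 for the intervention arm:

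E(Y) = b0 + b1·(2 weeks) + b2·(3 months) + b3·g·(2 weeks) + b4·g·(3 months)

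That is five fixed effects. I treat the assessment after 3 months as the 3-month occasion.

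- *Both arms, all three times.* The distinct rows are (1,0,0,0,0), (1,1,0,0,0), (1,0,1,0,0), (1,1,0,1,0) and (1,0,1,0,1). The rank is 5 of 5 and the model can be fitted.
- *Trained nurses, after 3 months only.* The single distinct row is (1,0,1,0,1). The rank is 1 of 5. Only the sum b0 + b2 + b4 is estimable, so there is no group effect and no group-by-time effect.
- *Both arms, after 3 months only.* The rows are (1,0,1,0,0) and (1,0,1,0,1). The rank is 2 of 5. Their difference isolates b4, so a cross-sectional contrast exists. But b1 and b3 are not estimable, there is no baseline, and with one occasion per nurse the between-nurse variance cannot be separated from the residual.

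The three interview rounds do not rescue the schedule. All are placed after 3 months, so none supplies a baseline or 2-week value.

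**3. Observation.** It is named in Primary Outcome. Its only description, in Process of Implementation, sits in the sequence of intervention-group steps and is tied to the impact of the course. No observer is named. The primary model is written for the NoMAD score, and the mixed-model sentence above covers secondary outcomes only. The sole basis for comparing observation between arms is the general statement in Statistical Analysis.

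**4. Blinding.** The main investigator announces allocation (Screening for Eligibility and Enrollment), follows up module completion, sends certificates and measures the toolkit variables (Process of Implementation), and interviews (Interview Procedure). None of this is compatible with that person being blind. The Randomization section defines code T as intervention and code C as control, and the Blinding section puts the same letters in the analysis data set. A supervisor-held key protects little when the codes themselves state the allocation.

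**The case against.** Several points on the other side stand.

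- A reader might infer that there are 0 of 86 control nurses and no baseline values at all. The document does not establish that. The Interviews text includes every participating nurse, the Outcomes section schedules all outcomes three times, and Data Collection mentions two forms at baseline without identifying the second. The zero count holds only on the completer reading.
- A reader might infer that the unblinded main investigator does the workplace observation and that it is to enter a mixed model. Neither is stated.
- A reader might infer that limiting interviews to completers breaks the randomization. It does not touch the randomized NoMAD comparison, which is analysed by intention to treat and sent to both arms at 3 months. The interviews are meant to explore views, and the Ethics Approval section already speaks of a process evaluation.
- The Blinding section says participants are unblinded and speaks of blinded examination and interpretation, so the label in Trial Design can be read as analyst blinding. NoMAD is a self-completed web questionnaire, with a telephone option only for non-responders, so assessor blinding matters little for it.
- Toolkit scoring may be left to a fuller document.

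These points narrow the concern but do not remove it. Even if all nurses are interviewed, the timing still contradicts the schedule and the model. Reading the blinding as analyst-only still conflicts with the stated blinding of the main researchers and is undone by the T and C codes.

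**Conclusion.** The concern holds in this form. The schedule and model for the secondary outcomes contradict the described interview and toolkit procedures. As described, the repeated-measures model cannot be fitted: rank 1 of 5 if only trained nurses are assessed after 3 months, rank 2 of 5 if both arms are. On the first reading, which the purpose and questions favour, no between-group effect can be estimated. Both ranks rest on the shared-baseline coding above and on timing the interviews and toolkit only after 3 months. Observation cannot support a between-group primary result as described. The blinding label is contradicted by the main investigator's documented tasks, and the codes reveal allocation to those interpreting the results. The NoMAD comparison stands, so the matter should be corrected but does not undermine the trial's main randomized result.

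**What to change.** - Reconcile Process of Implementation, Outcomes, Interview Procedure, Interviews and Statistical Analysis on who is assessed, when and by whom.
- Name the NoMAD score as the sole primary endpoint for the between-group test.
- Report interviews, context examination, toolkit and observation as descriptive process evaluation, and delete the mixed model for them.
- In Trial Design and Blinding, state that participants and the main investigator are unblinded and that only the analysts are blinded. Replace T and C in the analysis file with neutral codes A and B, with the key held by the supervisors until interpretation is final.

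The cost is rewording and recoding one variable, plus the loss of any confirmatory secondary comparison. The abstract says first outcomes became available in December 2020, so narrowing the primary outcome should be dated and explained. Any toolkit baselines that were not collected cannot be recovered.

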### Sample Size

The study has been designed as a superiority trial with 2 parallel groups (ELNEC-PPC web-based training plus usual care and usual care only). For calculation of the appropriate sample size, the main researcher uses the assumption that the 5 selected settings have 254 nursing staff members on average eligible for inclusion based on a survey of all included settings before the study to determine the total number of nurses who work in the selected settings and are appropriate for inclusion. Based on this assumption, as well as a 2-sided *P* value <.05, a 0.90 power, a traditional predictable correlation between 2 measurements of 0.5, and an intraclass correlation coefficient with *P*<.05, 86 participants were required in the intervention group and 86 were required in the control group for *t* tests. To support equal sample sizes, including for the units of the selected settings, and to account for intrastratified correlations of units, a multilevel analysis will be used. Nursing staff members who are transferred to a dissimilar organization unit will be exchanged from the sample of nursing staff, and changes will take place in the course of the study. To catch up with nursing staff members who are not changed in time, the researchers will insert an additional organization unit from the critical care units for the intervention and control groups, which will result in a total of 172 nursing staff members. All power analyses will be performed using the G*Power software (version 3.1).

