In the CNEU, randomization will be performed. If randomized to the ELNEC-PPC web-based training course in addition to usual care (intervention group), participants will be sent a link to the website that has all instructions for enrolling and registering in the training course and assistance on how to maintain access via instant messaging or email. Moreover, participants will be given information about their follow-up assessments and how to contact the main investigator if needed. If a participant declines to participate, the main investigator will ensure that the information from the baseline questionnaire is deleted. If randomized to usual care, participants will be instructed on the principles of usual care and will be given the same information as provided to the intervention group about their follow-up assessments and how to contact the main investigator if needed. The flow of participants through the trial is described in Figure 1.

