### Statistical Analysis

Results will be stated according to the CONSORT declaration concerning health [49,50]. The analysis of primary data will follow the intention-to-treat principle and relate the alterations in the overhead outcome measures between the intervention and control groups. SPSS Version 26.0 software (IBM Corp) will be used for the data analysis. Descriptive statistics will be presented by percentage distributions and indicators describing the location (arithmetic mean=M) and deviation (range; standard deviation=SD). The analysis of primary data will predict the mean difference with 95% CI in the NoMAD score at the 3-month follow-up between the intervention and control groups.

The model includes accessible data of nurse participants at all time points (ie, starting point, and after 2 weeks and 3 months). Within the regression model, distinct participants will be considered using a random effect approach, accounting for inside topic covariance construction. The group and time effects will be considered with asset effects using a combined intervention and time variable. Starting point levels will be obtained over 2 research collections supposing that starting point alterations are coincidental [66]. This is aimed at minimal starting point changes in the outcome variable.

Both groups will primarily be labeled according to their starting point features. The initial data will be analyzed to evaluate the effectiveness of ELNEC-PPC web-based training in the intervention group when compared with the findings in the control group, according to the NPT.

The analysis will inspect intervention effects continuously over time, and will assess the interaction between period and group allocation. The difference between the groups will be assessed for the period of the basic model and will be further evaluated according to the stratification by unit category (critical care unit and noncritical care unit) [67].

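### Swapping out transferred nurses during the study, and deleting decliners' baseline data, contradicts the stated intention-to-treat analysis

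*Protocol article*

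**What the plan says.** **Analysis population.** Statistical Analysis: "The analysis of primary data will follow the intention-to-treat principle".

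**Transfers.** Sample Size: "Nursing staff members who are transferred to a dissimilar organization unit will be exchanged from the sample of nursing staff". On timing, the same sentence adds that "changes will take place in the course of the study". For nurses not swapped in time, "the researchers will insert an additional organization unit from the critical care units for the intervention and control groups", which brings the total to 172. How substitutes, or nurses in the added unit, receive an allocation is not described.

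**Decliners.** Screening for Eligibility and Enrollment, in the text after Figure 1: "If a participant declines to participate, the main investigator will ensure that the information from the baseline questionnaire is deleted". The paragraph holding this sentence opens its arm-specific instructions with "If randomized to the ELNEC-PPC web-based training course in addition to usual care (intervention group), participants will be sent a link to the website", and the usual-care instructions come after the deletion sentence. The deletion rule is not repeated there.

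**Order of steps.** The same section has consent signed and the baseline link sent first: "Then, randomization will be performed via a web-based randomization system". The main investigator then contacts nurses to "inform them about the results of the random distribution, and provide instructions according to the group that was randomly chosen". The Randomization section, by contrast, mentions completion of baseline assessments after the allocation envelopes are opened. The Blinding section confirms that nurses know their arm.

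**The concern.** Intention-to-treat means that every randomized nurse is analysed in the arm to which she was allocated. Exchange takes randomized nurses out of the sample and brings in others with no described random allocation. Deletion leaves a nurse who declines with no data at all. If either happens after nurses know their arm, the groups compared are no longer the groups that were randomized.

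The direction could favour the course. Nurses unwilling to take it may also be those who would report less normalization of palliative care, and the deletion sentence is written under the course arm only. The mixed model in Statistical Analysis also appears to treat baseline differences between arms as chance. Randomization justifies that assumption, and arm-dependent removal or substitution weakens it.

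Transfers are foreseeable. The eligibility criteria screen out nurses expected to move, but the abstract still names transfer as a cause of dropout, and the Discussion calls a high dropout rate likely.

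**Working it through.** **1. The passages side by side**

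- *Exchange against intention-to-treat.* Exchange is expressly placed during the study, so it is not confined to the time before randomization. The Randomization section describes one set of coded forms, sized to the sample, and no later draw for substitutes. The two statements conflict as written.
- *Deletion against intention-to-treat.* If baseline precedes randomization, as the enrollment text says, and the sentence is read where it stands, a nurse can learn her arm, decline the course and have her data removed. If the order in the Randomization section holds, the sequence is different. The timing is therefore unsettled, but no text limits deletion to the time before randomization.
- *The mixed model.* It uses the available data of participants at all time points. It can accommodate missed visits of nurses who are retained. It cannot restore nurses who were removed, or make substitutes randomized.

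**2. Is there room for losses in 86 per arm?**

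Stated inputs (Sample Size): two-sided 0.05, power 0.90, correlation 0.5, t tests, 86 per arm. No effect size or SD is given, so 86 cannot be derived from the stated inputs alone. Assume a standardized difference d = 0.5:

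- Normal approximation: n = 2(1.960 + 1.282)² / 0.5² ≈ 84.1, so 85 per arm.
- Two-sample t calculation: 85.03, so 86 per arm, with power 0.903 at 86.
- Solving backwards from 86 per arm and power 0.90: d = 0.497.
- Using the correlation of 0.5 to reduce the variance by the factor 1 − 0.5² = 0.75 gives 64 per arm, which does not match.

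So 86 matches an unadjusted t test at d = 0.5 with nothing added for loss. Exchange and the added unit are what the section relies on to hold the number.

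**3. Size of the bias (assumed rates)**

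Let a fraction f of the course arm be removed, with a mean g SD below those kept, and be replaced by nurses like those kept. The shift in the arm mean is b = f × g. With no true effect and 86 per arm, SE = √(2/86) = 0.1525 SD, and the type I error is 1 − Φ(1.96 − b/SE) + Φ(−1.96 − b/SE).

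| f | g (SD) | Shift b (SD) | Type I error |
|---|---|---|---|
| 5% | 0.25 | 0.0125 | about 0.051 |
| 10% | 0.5 | 0.05 | about 0.062 |
| 20% | 0.5 | 0.10 | about 0.10 |

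A shift of 0.10 SD is 0.10/0.5 = 20% of the assumed d.

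**4. Power if nobody is replaced (assumed d = 0.5, 86 randomized per arm)**

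- 10% loss: 77 per arm, power 0.869.
- 20% loss: 69 per arm, power 0.830.
- 30% loss: 60 per arm, power 0.775.

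**The case against.** Several stronger readings are tempting, and the text does not carry them.

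- *That intention-to-treat cannot be performed.* Sample Size does not say that a transferred nurse's data are discarded. If she is followed and analysed as randomized, the analysis is recoverable. What stands is that the plan contradicts itself.
- *That substitutes are known not to be randomized.* This would be read from silence. What stands is that no allocation route is described for them.
- *That deletion is certainly one-sided and after randomization.* The sentence names no arm and could be an ordinary commitment on data withdrawal. The one-sided reading rests on where the sentence stands, and the order of baseline and randomization is itself inconsistent. What stands is that the wording permits an arm-specific exclusion.
- *That the effect is certainly inflated.* Nurses who are uninterested or expected to move are ineligible, nurses have a week to decide, and the Discussion reports very good readiness to join. Removal may be rare. The bias also comes from missing 3-month outcomes, so a retained baseline corrects it only in part if the nurse gives no follow-up.
- *That transfer never prevents measurement.* The NoMAD questionnaire can be sent electronically or taken by telephone. But the primary outcome also includes observation of routine care, and monitoring and interviews take place at the workplace. NoMAD items on using the intervention at work may also fit less well after a move. This stands as a limit on the fix.

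An unseen analysis plan would not remove the point. The conflict is between statements in the protocol itself, and a later plan could not restore erased data.

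**Conclusion.** The concern holds as a contradiction within the protocol. Exchanging nurses while the study runs, with no stated random allocation for substitutes, does not fit the declared intention-to-treat analysis. The deletion rule, as placed, permits an arm-specific exclusion after randomization. The transfer part rests on explicit wording. The decliner part is less certain, because its timing and arm must be inferred.

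The size is unknown: the documents give no transfer or decline rates, and the assumed values run from negligible to a doubling of the type I error. That every effect estimate from this trial would be seriously biased does not follow. The finding that 86 per arm holds no allowance for loss depends on the assumed d = 0.5.

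**What to change.** - **Sample Size.** Delete the exchange and added-unit rule for nurses already randomized, and allow replacement only before randomization. Follow transferred nurses with NoMAD by e-questionnaire or phone to 3 months and analyse them in their randomized arm.
- **Screening for Eligibility and Enrollment.** Limit deletion to nurses who decline before randomization or who withdraw consent for data use. Apply the same rule in both arms, and still invite those who decline the course to the follow-up NoMAD.
- **Statistical Analysis.** Define the primary set as all randomized nurses in the mixed model already planned.
- **Order of steps.** Reconcile the enrollment text with the Randomization section on whether baseline comes before or after allocation.
- **Events to date.** Recruitment opened in July 2020 and first outcomes are dated December 2020, so rewording alone may not be enough. Report by arm any exchange or deletion already made and, where the data remain, reverse it in the analysis.

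**Cost.** There will be fewer complete cases, reliance on a missing-at-random assumption, possible loss of workplace observation after a transfer, and lower power (at an assumed d = 0.5, about 0.87 at 10% loss and 0.83 at 20%). The protocol should state this loss of power. For scale, holding 86 complete cases per arm would take 86/0.9, so 96 per arm, at 10% loss, and 86/0.8, so 108 per arm, at 20%.
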